#### Primary and secondary study outcomes

2.4.3.

Primary outcomes are the Neurobehavioral Symptom Inventory (NSI), Patient Global Impression of Change (PGIC), and Functional Near-infrared Spectroscopy (fNIRS). These primary outcomes represent different domains of function that are commonly affected following mTBI and provide different sources of information about the injury that inform clinical care decisions (i.e., treatment and/or rehabilitation). The NSI gathers specific information about mTBI symptoms. This measure is comprised of 22 items scored from 0 to 4 (0 total score represents no mTBI-related symptoms, 88 total score represents very severe levels of all 22 mTBI-related symptoms). The PGIC captures patient self-reported assessment of changes in their overall quality of life throughout their mTBI recovery. The prompt for the PGIC is: “Since beginning treatment at this facility, how would you describe the change (if any) in activity limitations, symptoms, emotions and overall quality of life related to your post-concussive condition?” The patient responds on a scale ranging from 0 (No change or condition has gotten worse), to 7 (A great deal better and a considerable improvement that has made all the difference). The fNIRS is a non-invasive imaging tool that measures changes in cerebral blood flow (CBF) and oxygenation in response to a behavioral task. The current study utilizes three neurocognitive tasks (WAIS symbol search and coding, and a flanker task) and a resting condition. Brain activation and deactivation in brain regions of interest (ROIs) will be examined and compared between groups within the first week following enrollment and at approximately four-weeks after enrollment. Secondary outcomes will include data from symptom, neurocognitive, balance, vestibular, sleep, and physical activity assessments (see Table 2). In addition, participant demographics and medical history data will be gathered as part of the normal clinical interview for mTBI (e.g., age, sex, history of mTBI, migraine). A daily text message-based assessment will be used to evaluate each participant’s compliance with their assigned intervention; and to assess frequency and intensity of at-home exercises in between the initial, 2-, and 4-week in-person study intervals. A FitBit Inspire 2 activity monitor will be provided to each participant to track activity and sleep throughout the 4-week intervention period. A detailed description of all study measures, scoring, and validity is presented in Supplemental material (see Description of Measures).

**Table 2 tab2:** Assessments used for primary and secondary outcomes.

Primary outcomes	Secondary outcomes
Neurobehavioral Symptom Inventory (NSI)	Behavioral Symptom Inventory (BSI-18)
Patient Global Impression of Change (PGIC)	Dizziness Handicap Inventory (DHI)
Functional Near-infrared Spectroscopy (fNIRS)	Vestibular/Ocular Motor Screening (VOMS)
	Modified Balance Error Scoring System (mBESS)
	Functional Gait Assessment (FGA)
	Clinical Profile Screening (CP-Screen)
	Immediate Post-concussion Assessment and Cognitive Testing (ImPACT)
	Pittsburgh Sleep Quality Index (PSQI)
	Headache Impact Test (HIT-6)
	ID Migraine
	Short-form McGill Pain Questionnaire (SF-MPQ)
	International Physical Activity Questionnaire (IPAQ)
	Buffalo Concussion Bike Test (BCBT)

#### Interventions for adjudicated concussion clinical profiles and usual care groups

2.4.4.

Participants assigned to the T-MD Intervention Group will be prescribed one or more of the intervention domains described in the following sections based on the results of the adjudication process. For example, one participant may be prescribed interventions for anxiety/mood, ocular, and vestibular domains, whereas another participant may be prescribed interventions for anxiety/mood, sleep, and autonomic domains. Each prescribed intervention will be tailored to the specific affected domains and sub-domains, based on clinical consensus (5). For example, within vestibular interventions, one participant may be prescribed only dynamic balance interventions, whereas another participant may be prescribed dynamic gait, gaze stability, and dynamic balance interventions. We will track the specifics of each participant’s intervention to evaluate individual intervention effects. T-MD interventions will be prescribed for a 4-week treatment period (See Description of TMD Interventions document presented in Supplemental material). The participants in the usual care intervention group will be prescribed standardized behavioral management strategies related to activity, sleep, hydration, nutrition, and stress (See Description of Behavioral Regulation Strategies document in Supplemental material).

#### Return to activity/recovery

2.4.5.

Return to activity will be medical clearance to resume full activities based on participant being symptom and/or impairment free at rest, and symptom free following standardized exertion protocols per recent consensus (16). We will assess RTA at 4 weeks and 3 months post-intervention.

#### Healthcare utilization and costs

2.4.6.

Throughout the trial we will record the number of costs incurred by the patient during their clinical care for mTBI including numbers and types of providers involved, CPT codes charged, and the number of work/school absences reported by each participant enrolled into the trial. All CPT coding will be entered from data within each participating hospital system. The CPT codes will include any within-system referrals that the clinical team provides as part of their care. Any care that happens outside of the participating healthsystems, which is rare, will be recorded by the research team.

### Procedures

2.5.

Potential participants with a suspected complex mTBI will be identified during their initial clinic evaluation. Treating clinicians, and a member of the clinical research team, will administer the screening measures as part of their standard clinical exam. At the end of the exam, eligible participants will be informed if they qualify for the study and if they demonstrate interest, they will be referred to an on-site research coordinator. If an eligible individual is not interested, the treating clinician will complete their standard of care treatment plan. Interested participants will be enrolled, consented, and scheduled to complete the initial comprehensive clinical outcome assessments (baseline assessment), including primary and secondary outcome measures, within 5–7 days of study enrollment. After randomization, the participant’s treating clinician will describe the study treatment interventions based on the participant’s group assignment. Participants will be provided detailed instructions and demonstrations of all assigned interventions. At this initial timepoint, research staff will onboard participants for daily text message reminders that will enable participants to self-report daily compliance (yes/no) for completion of their assigned interventions for the 4 weeks of study participation. Text message reminders and self-reported compliance will also be distributed to the usual care group regarding the adherence with behavioral regulation activities (e.g., practice good sleep hygiene).

After the initial clinical evaluation and randomization into treatment or usual care groups, the clinical research team will adjudicate each participant’s complex mTBI diagnosis. Participant symptoms, impairments, and clinical exam/interview findings will be discussed to substantiate the presence of symptoms/impairments in each of the complex mTBI domains. An adjudication checklist will be completed during this process along with additional information from the clinical exam and interview. At the conclusion of the review and discussion, group consensus will be used to confirm each participant’s complex mTBI profiles and the final clinician-adjudicated and assessment-identified complex mTBI domains will be used to inform the targeted interventions for participants assigned to the T-MD group. At any point during the 4-week intervention of the study, domains can be updated and changed by treating clinicians. The adjudication process is based on the process developed in our TEAM-TBI work (22). A timeline of the study procedures and assessments is summarized in Figure 1. We will also tabulate each participant’s healthcare utilization and related costs using EHR at the conclusion of participation in the study protocol. We will also determine if participants are recovered (i.e., medically cleared for full return to activity) at 4 weeks and 3 months post-intervention.

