**Methods:**

This study employs a single-blinded, two-group repeated measures design. The RCT will enroll up to 250 military-aged civilians (18-49 yrs) with a diagnosed complex mTBI within 8 days to 6 months of injury from two concussion specialty clinics. The two study arms are a T-MD intervention and a usual care, behavioral management control group. All participants will complete a comprehensive, multidomain clinical evaluation at their first clinical visit. Information gathered from this evaluation will be used to adjudicate mTBI clinical profiles. Participants will then be randomized to either the 4-week T-MD or control arm. The T-MD group will receive targeted interventions that correspond to the patient’s clinical profile (s) and the control group will receive behavioral management strategies. Primary outcomes for this study are changes from enrollment to post-intervention on the Neurobehavioral Symptom Inventory (NSI), Patient Global Impression of Change (PGIC), and functional near-infrared spectroscopy (fNIRS). Time to return to activity (RTA), and healthcare utilization costs will also be assessed.

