### Allocation to study arms

2.2.

Participants will be screened and recruited from two concussion specialty clinics, and randomization will be stratified by site. Within site, a permuted block randomization with random block sizes with a 1:1 allocation ratio will be used. The lead biostatistician will generate the randomization list which will be uploaded into the electronic data capture system. The site coordinator will receive the allocation for each participant once all eligibility information is entered and the participant is deemed eligible for the trial. Participants will be randomized to either the T-MD or usual care intervention arm. Treating clinicians and study research staff will not be blinded to participant group, as they will be employing study procedures and supervising participants in the study. The Principal Investigators will be blinded to participant group assignment throughout the study, including during data analysis.

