Inclusion criteria are age 18–49 years, normal/corrected vision, and diagnosed with a currently symptomatic mTBI with a clear mechanism of injury in the past 8 days-6 months. In addition, participants will have complex mTBI symptoms and/or impairments in at least one of the following domains: anxiety/mood, cognitive, migraine, ocular, vestibular, sleep, autonomic; per a comprehensive assessment, clinical exam/interview, and adjudication process. Exclusion criteria for this study include history of vestibular disorder (e.g., benign paroxysmal positional vertigo, unilateral or bilateral vestibular hypofunction), history of neurological/mental health disorders (e.g., epilepsy, seizure disorders, schizophrenia, bipolar), history of brain surgery/malformations/tumors, diagnosed with cardiac, peripheral or cerebrovascular disease, experienced chest pain or shortness of breath while at rest or with mild exertion, been told by a doctor to only conduct physical activity under medical supervision, previous moderate to severe TBI, <8 days- or > 6 months following current complex mTBI, currently pregnant or become pregnant during study, and/or currently involved in litigation associated with current or previous mTBI, currently on workman’s compensation, previously participated in the study, or previously received clinical concussion care at either participating site within the last 2 years. Participants with a history of mTBI, attention deficit hyperactivity disorder (ADHD), learning disability (LD), migraine, or motion sickness will not be excluded, which will more closely reflect the true characteristics of this population and increase the external validity of the study results.

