#### Complex mTBI diagnosis criteria

2.4.2.

The complex mTBI diagnosis will be defined as persistent mTBI symptoms that are associated with observable clinical impairments lasting more than a week following injury. The domains and assessments that will be used to screen for complex mTBI are documented in Table 1 below. Participants must demonstrate a positive finding in at least one of the complex mTBI domains to be considered for enrollment into the study. Tests from the NIH Common Data Elements (CDE) (21) set for sport-related concussion will be utilized when available.

**Table 1 tab1:** Assessments for determining complex mTBI domains.

Domain	Positive findings/indication for enrollment
Anxiety/Mood	Global Severity Index (GSI) T-score > 50; or CP-Screen Anxiety(A)/Mood(M) Avg score ≥ 2 or 1+ individual item = 3 BSI-18 subscale T score ≥ 63 (Overall, A, M) **Subdomains**: Anxiety (A):  Mood (M):  Both (M/A): 
Cognitive	≤7^th^% on one or more ImPACT composite scores; or CP Screen Cognitive Avg score ≥ 2 or 1+ individual item = 3; AND ≤ 30 on ImPACT Impulse Control; AND < 9 on REY 15
Migraine/ Headache	≥2 on ID Migraine- migraine (M); or ≥ Grade 2 (≥ 50) on HIT-6- headache (HA); or CP-Screen Migraine Avg score ≥ 2 or 1+ individual item = 3 **Subdomains**: Headache (HA) Only:  Both (M/HA):  Migraine (M) with ocular/light sensitivity:  Migraine (M) with noise sensitivity:  Migraine (M) with motion sensitivity: 
Ocular	≥2 on smooth pursuits or hor/ver saccades, or near point convergence (NPC) ≥10 cm; or CP-Screen Ocular Avg score ≥ 2 or 1+ individual item = 3
Vestibular	≥2 on vestibulo-ocular reflex (VOR) and/or visual motion sensitivity (VMS); or > 9 total errors on mBESS; or CP-Screen Vestibular Avg score ≥ 2 or 1+ individual item = 3
Sleep	≥5 on PSQI global score, or CP-Screen Sleep Avg score ≥ 2 or 1+ individual item = 3
Autonomic	Increase of 3+ (from resting value) on VAS; or Unable to complete BCBT per patient or clinician

Clinical Profiles Screen (CP-Screen), Brief Symptom Inventory-18 (BSI-18), Immediate Post-Concussion Assessment and Cognitive Testing (ImPACT), REY15-Item Memorization Test (REY 15), Headache Impact Test-6 (HIT-6), Pittsburgh Sleep Quality Index (PSQI), Visual Analogue Scale (VAS), Buffalo Concussion Bike Test (BCBT).

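### Section 2.5 adjudicates the complex mTBI diagnosis after randomization, with unblinded staff, although the abstract and Section 2.3 place adjudication before it

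*Protocol article*

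**What the plan says.** The protocol article describes the step in four places.

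- Abstract, Methods: information from the first-visit evaluation "will be used to adjudicate mTBI clinical profiles. Participants will then be randomized".
- Section 2.3 (eligibility): inclusion requires "complex mTBI symptoms and/or impairments in at least one of the following domains", established "per a comprehensive assessment, clinical exam/interview, and adjudication process".
- Section 2.2 (allocation): the site coordinator receives the allocation "once all eligibility information is entered and the participant is deemed eligible for the trial". The same section says "Treating clinicians and study research staff will not be blinded to participant group"; only the Principal Investigators are blinded.
- Section 2.5 (Procedures): "After the initial clinical evaluation and randomization into treatment or usual care groups, the clinical research team will adjudicate each" person's complex mTBI diagnosis. A group consensus then confirms the profiles, and the resulting domains guide treatment in the T-MD arm.

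Section 2.4.2 defines the diagnosis as "persistent mTBI symptoms that are associated with observable clinical impairments lasting more than a week following injury". It introduces Table 1 as "The domains and assessments that will be used to screen for complex mTBI" and requires at least one positive domain before a person is considered for enrollment. Section 2.5 also says that patients learn at the end of the clinic exam whether they qualify.

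**The concern.** Adjudication confirms who belongs to the study population and which domains are affected. If it is part of eligibility, it has to be finished before allocation. Done afterwards by people who know the arm, it can no longer be taken as an arm-neutral baseline classification.

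The stakes for the adjudicators also differ by arm. Section 2.4.4 bases the T-MD prescription on the adjudicated domains, whereas usual care is a standardized package. Finding or not finding a domain changes treatment for a T-MD participant and nothing for a control. Staff who know the arm therefore have a reason, even an unconscious one, to look harder for domains in one arm. Any later use of those domains as baseline information would carry that difference.

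**Working it through.** No figure in the plan states this point, so the check is mainly a comparison of the text.

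**1. Order of steps**

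- Abstract: evaluate, adjudicate, randomize.
- Sections 2.3 and 2.2 together: adjudication helps establish inclusion, and inclusion must be complete before the allocation is released. The order is again adjudicate, then randomize.
- Section 2.5: evaluate, randomize, adjudicate.

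The third order conflicts with the other two. The abstract speaks of profiles and Section 2.5 of the diagnosis, but Section 2.5 confirms the profiles in the same meeting, and enrollment needs at least one positive domain. It is the same process.

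**2. Which text could give way**

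If the exam and Table 1 settle eligibility (Sections 2.4.2 and 2.5), later adjudication only refines the diagnosis and plans treatment. The abstract and Section 2.3 then need correcting. If Section 2.3 is right, Section 2.5 needs correcting. No reading leaves all four places intact.

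**3. Knowledge of the arm**

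The adjudicators are the clinical research team. The panel is not listed and could include blinded Principal Investigators, but the team falls within the roles that Section 2.2 calls unblinded. No procedure for withholding the arm is described.

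**4. Where the classification could matter**

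- Section 2.6 compares baseline characteristics by arm and adjusts for differences in secondary analyses. If adjudicated domains were counted among those characteristics, an imbalance could reflect adjudication rather than chance.
- Section 2.6 explores factors, including impairments, that may modify the effect on NSI, PGIC and RTA. Domains used there would have been assigned with the arm known.
- Section 2.5 lets treating clinicians change domains at any time in the 4 weeks, so the final list is not a baseline list.

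**5. Possible dilution of the NSI comparison**

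Inputs from Section 2.6: a difference of 5 points, 80% power, two-sided alpha 0.05. The stated power is taken at face value, not re-derived. Assumption: a share q of T-MD participants has no confirmed domain, stays in the analysis and gains nothing. The documents give no q.

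- Implied standard error: 5 / (1.96 + 0.8416) = 1.785.
- By construction this returns the plan's figure: Phi(5/1.785 − 1.96) = 80%.
- Diluted effect: 5 × (1 − q). Power: Phi(effect/1.785 − 1.96).

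| q (assumed) | Effect (NSI points) | Power |
|---|---|---|
| 2% | 4.9 | 78.4% |
| 5% | 4.75 | 75.9% |
| 10% | 4.5 | 71.3% |

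Table 1 is wide, and every enrolled person already has a positive finding, so q is probably at or below the low end. The 10% row is an outer bound.

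**The case against.** The strongest reply is that eligibility is settled before randomization. Patients are told at the end of the exam whether they qualify, Table 1 gives enrollment cut-offs, and Section 2.2 releases the allocation only afterwards. The abstract is condensed, and Figure 1, to which Section 2.5 refers for the timeline, is not available here. This stands as the better-supported reading, but it moves the error to the abstract and Section 2.3 and leaves the domains confirmed with the arm known.

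Second, a T-MD participant with nothing to treat is largely hypothetical. Section 2.5 counts domains identified by assessment as well as those adjudicated by clinicians, and everyone enrolled has at least one of the former. If either source suffices, q is about zero. This also stands, and it is why the dilution table shows only what could happen.

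Third, Section 2.6 does not say that adjudicated domains will be the exploratory factors. Its analysis of treatment domains is confined to the T-MD arm, where knowledge of the arm cannot differ, and Section 3.3 disclaims power for domain effects. The exploratory concern is therefore conditional on adjudicated domains being used as factors in the between-arm analysis.

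**Conclusion.** The contradiction is real and lies within the current text. As Section 2.5 stands, the diagnosis and domains are confirmed after allocation, with no arrangement to keep the arm from the adjudicators. The consequence is a risk of arm-aware classification, which would affect a by-arm description of domains or a factor analysis that uses them. For the NSI comparison it means at most slight dilution, and possibly none.

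A reader might infer that unconfirmed T-MD participants would be withdrawn, leaving a more impaired T-MD group and a spurious advantage. The documents do not support this. No section removes anyone after adjudication, and Section 2.6 specifies intention to treat and a mixed model over all visits. The complete-case wording there is part of the sample-size allowance.

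A reader might also infer that Section 2.3 should be narrowed to observable impairments to match Section 2.4.2. That does not follow: anxiety/mood, migraine/headache and sleep have only questionnaire criteria in Table 1, so a strict reading could exclude patients whom the trial means to treat.

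The correction is worth making because it is cheap. Confidence is moderate, since the panel's membership and the unconfirmed share are not given.

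**What to change.** Preferred: complete and lock the adjudication checklist and consensus before the allocation is released, treat them as part of the eligibility information in Section 2.2, and correct Section 2.5 to match.

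If that is not workable in clinic, and for participants already randomized:

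- adjudicate from the screening records with the arm withheld;
- state in the abstract and Section 2.3 that the exam and Table 1 settle eligibility;
- keep every randomized participant in follow-up and analysis, whatever adjudication finds;
- report the number not confirmed, by arm.

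In either case, use only domains fixed before allocation, or adjudicated with the arm withheld, as factors in the Section 2.6 exploratory analysis. Later updates by treating clinicians can guide care but should not replace them.

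Cost: no new assessments. The T-MD prescription already depends on adjudication, so the added wait falls mainly on controls. Section 3.2 sends the first text, with details of the assigned intervention, the day after enrollment, so the start of the daily texts would have to be aligned with the later allocation. A few people would be adjudicated and then not randomized.

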**Figure 1 fig1:**
[figure not shown]
Study procedures for recruitment, screening, randomization, and outcomes assessment timelines for intervention/control groups. Anxiety (Anx), Brief Symptom Inventory-18 (BSI-18), Buffalo Concussion Bike Test (BCBT), Clinical Profiles Screen (CP-Screen), Current Procedural Terminology (CPT), Dizziness Handicap Inventory (DHI), Functional Gait Assessment (FGA), Functional Near Infrared Spectroscopy (fNIRS), Headache (HA), Headache Impact Test-6 (HIT-6), Immediate Post-Concussion Assessment and Cognitive Testing (ImPACT), International Physical Activity Questionnaire (IPAQ), Loss of Consciousness (LOC), Mild Traumatic Brain Injury (mTBI), Modified Balance Error Scoring System (mBESS), Pittsburgh Sleep Quality Index (PSQI), Return to Activity (RTA), REY15-Item Memorization Test (REY 15), Short-Form McGill Pain Questionnaire (SF-MPQ), Vestibular Ocular Motor Screening (VOMS), Visual Analogue Scale (VAS).

